### Schematic representation:

[figure not shown]

**Treatment:**

Validated Yoga Module for 2 weeks (10 supervised sessions over 2 weeks- 45minutes/session)  
(Developed by [name] et al., 2021 at NIMHANS)

The module to be taught and practiced under the supervision of a trained Yoga therapist only.

Yoga module for substance use disorder during Acute withdrawal phase.

| S.no                 | Practice (Sanskrit)                                     | Practice (English)            | Rounds | Time (minutes) |
|----------------------|---------------------------------------------------------|-------------------------------|--------|----------------|
| RELAXATION TECHNIQUE |                                                         |                               |        |                |
| 1.                   | Takshan shithalakaran upaya                             | Instant Relaxation Technique  | 2      | 4              |
| BREATHING PRACTICES  |                                                         |                               |        |                |
| 1.                   | Pawanmuktasana kriya                                    | Wind releasing pose breathing | 5      | 5              |
| 2.                   | Udarashvasana kriya                                     | Deep abdominal breathing      | 5      | 2              |
| 3.                   | Makarasana shvasana kriya                               | Crocodile pose breathing      | 5      | 2              |
| 4.                   | Bhujangasana shvasana kriya                             | Cobra pose breathing          | 5      | 2              |
| 5.                   | Naukasana shvasana kriya                                | Boat pose breathing           | 5      | 2              |
| 6.                   | Marjariasna kriya                                       | Tiger stretch breathing       | 5      | 2              |
| SPECIFIC ASANAS      |                                                         |                               |        |                |
| 1.                   | Uttana padasana                                         | Straight leg raising          | 5      | 2              |
| 2.                   | Titili asana                                            | Butterfly                     | 1      | 2              |
| 3.                   | Trikonasana                                             | Side bending                  | 5      | 2              |
| SECTIONAL BREATHING  |                                                         |                               |        |                |
| 1.                   | Vibhagiya pranayama                                     | Chin mudra                    | 5      | 2              |
| 2.                   | Vibhagiya pranayama                                     | Chinmaya mudra                | 5      | 2              |
| 3.                   | Vibhagiya pranayama                                     | Adi mudra                     | 5      | 2              |
| PRANAYAMA            |                                                         |                               |        |                |
| 1.                   | Nadishuddhi                                             | Alternate nostril breathing   | 9      | 3              |
| 2.                   | Bhastrika                                               | Bellows breath                | 2      | 2              |
| 3.                   | Bhramari                                                | Humming bee breath            | 9      | 2              |
| RELAXATION           |                                                         |                               |        |                |
| 1.                   | Sampurna vishranti paddati in shavasana with AUM chants | Deep relaxation technique     | 1      | 5              |

**Statistical analysis:**

- Data would be analyzed using R statistical software (Version 4.4.1). Based on the distribution and variance appropriate statistical tests will be used for analysis.
- Baseline continuous data will be analyzed using an independent sample t-test. Baseline categorical data will be analyzed using the chi-square test. Data will be checked for normality, for longitudinal analysis, a linear mixed model will be used.
- If the data is not normally distributed and the samples are small, a nonparametric test is appropriate, and to compare two groups Mann Whitney U test is performed.

- Primary longitudinal outcomes will be analyzed using Linear Mixed-Effects Models (LMM) with the lme4 package.
- Time to recovery from withdrawal symptoms will be analyzed using survival analysis.

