### **Methodology:**

- Age: 18 to 50 years.
- Sex: Both male and female.
- Sample size: 60 (30 patients in Yoga + Treatment as usual group and 30 patients in treatment only group).
- Source of Subject: Inpatient services run by the CAM & Department of Integrative Medicine, National Institute of Mental Health and Neurosciences (NIMHANS), Bengaluru, India

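### The statistical section lets the observed distribution choose between a mixed model and a Mann-Whitney test, so the analysis of COWS and HRV scores is not uniquely fixed in advance

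*Protocol*

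**What the plan says.** All the relevant text is in the protocol's Statistical analysis section. It opens with a general rule: "Based on the distribution and variance appropriate statistical tests will be used for analysis". For baseline comparisons it says "Baseline continuous data will be analyzed using an independent sample t-test". It then puts the check and the model in one sentence: "Data will be checked for normality, for longitudinal analysis, a linear mixed model will be used". The next bullet says "If the data is not normally distributed and the samples are small, a nonparametric test is appropriate", and continues that "to compare two groups Mann Whitney U test is performed". Two further bullets carry no condition: "Primary longitudinal outcomes will be analyzed using Linear Mixed-Effects Models (LMM) with the lme4 package" and "Time to recovery from withdrawal symptoms will be analyzed using survival analysis".

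Under Methodology the size is fixed: "Sample size: 60 (30 patients in Yoga + Treatment as usual group and 30 patients in treatment only group". The Study design section places assessments at baseline and at the end of the two-week intervention.

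**The concern.** Two instructions can apply to the same COWS and HRV scores. One makes the test depend on the distribution seen in the trial; the other names a mixed model outright. Nothing ranks them.

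The trigger is also open. There is no normality test or threshold, no statement of whether raw scores, changes or residuals are examined, and no list of outcomes or time points covered. Whether 30 per arm is small could be settled now, because the size is known, but it is left to judgement.

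This is more than detail deferred to a SAP. The protocol states a data-dependent rule, and a SAP written to it would inherit the ambiguity. Two things are at stake: freedom to pick the analysis after seeing results, and possible loss of the baseline measurement that the trial already collects.

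**Working it through.** **Inputs from the protocol.** 30 per arm; two assessments; baseline COWS limited to 4-24 (Inclusion criteria); withdrawal lasting 5 to 14 days (Introduction), which makes low scores at two weeks plausible. The protocol gives no alpha, power, effect size, SD, correlation or end-of-treatment distribution, so it has no figure to reproduce. Everything below rests on assumptions: two-sided 5%, an effect of 0.65 SD, and baseline-to-end correlation ρ of 0.3, 0.5 or 0.7.

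**1. Normal scores, by formula.** Baseline adjustment shrinks the SD by √(1−ρ²) = 0.954, 0.866, 0.714. The standardised effect becomes 0.65/0.954 = 0.68, 0.65/0.866 = 0.75 and 0.65/0.714 = 0.91. Power at 30 per arm is then 75%, 83% and 94%. A Mann-Whitney test on end scores (efficiency 0.955) has 69% whatever ρ is. The difference is about 6, 14 and 25 points.

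**2. Floored scores, by simulation.** Assumed: baseline mean 13, SD 5, limited to 4-24; end mean 5, SD 5 before flooring at zero. A group-by-time mixed model with two time points and no baseline constraint amounts to a comparison of change scores, so that is shown as well. Read the figures to within about 3 points.

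| Power, effect 0.65 SD | ρ = 0.3 | ρ = 0.5 | ρ = 0.7 |
|---|---|---|---|
| Baseline-adjusted (ANCOVA) | 68% | 76% | 87% |
| Mann-Whitney on end scores | 66% | 67% | 65% |
| Change score (unconstrained mixed model) | 41% | 53% | 72% |

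ANCOVA minus Mann-Whitney: 2, 9 and 22 points. ANCOVA minus change score: 27, 23 and 15 points. Mann-Whitney minus change score: +25, +14 and −7 points.

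**3. How often the rule would switch.** Using Shapiro-Wilk at 5% in either arm on raw end scores, the switch rate under the assumptions of step 2 was 87-100% with an end mean of 5 and about 11-28% with an end mean of 10. A separate set of simulations, 3,000 trials per scenario, varied the shape and what is checked:

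| Assumed shape of end scores | Check on raw end scores, by arm | Check on model residuals |
|---|---|---|
| Normal | about 9-10% | about 5% |
| Mild floor | 16-38% | 4-8% |
| Strong floor | about 100% | 21-89% |
| Right skew | about 100% | 88-99% |

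**4. Type I error.** In that second set, the two-stage rule (Mann-Whitney if the check on raw scores fails, otherwise ANCOVA) gave 4.3-5.9%. Taking the smaller of the ANCOVA and Mann-Whitney p-values gave 6.3-9.4%. Pairing Mann-Whitney with a change-score test instead, in simulations of 2,000 trials per cell, gave 8.4-10.5%.

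**The case against.** No sentence says that Mann-Whitney replaces the mixed model. The nonparametric bullet concerns comparing two groups, comes shortly after the t-test for baseline data, and is followed by an unconditional mixed-model bullet. On that reading Mann-Whitney merely stands in for the t-test. This reading is reasonable, but the opening rule is not limited to baseline data, and the normality check shares a sentence with the mixed model. The text supports both readings, and that is the defect.

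Four stronger readings are tempting and are not supported:

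- **That COWS will very likely switch.** The protocol gives no end-of-treatment distribution, and step 3 runs from about 5% to 100%.
- **That the rule inflates type I error.** Followed strictly it does not; the excess needs free choice between p-values, which the protocol does not propose but its undefined triggers permit.
- **That switching always loses power.** The loss is against a baseline-adjusted model. Against an unconstrained two-time-point mixed model, the rank test gains at ρ of 0.3 and 0.5 and loses only near 0.7. With right-skewed scores and ρ of 0.3, it lost nothing even against ANCOVA (64% against 62%). Nor need baseline be discarded: the test could be run on change scores, and the text does not say.
- **That the whole primary analysis is open.** Time to recovery is assigned to survival analysis.

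**Conclusion.** The point holds in a limited form. The protocol makes the choice of test depend on the trial's own data, with undefined triggers, beside an unconditional mixed model. The analysis of COWS and HRV scores is therefore not uniquely fixed before the data are seen.

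The harm is analytic flexibility (type I error of about 6-10% if the smaller p-value were chosen) and avoidable loss of power. Against a baseline-adjusted model, a rank test on end scores gives up about 2, 9 and 22 points at ρ of 0.3, 0.5 and 0.7; an unconstrained mixed model gives up about 27, 23 and 15. These sizes rest on the assumed floored distribution and 0.65 SD effect. That the text leaves the choice open rests on no assumption. Baseline adjustment is the better route under either reading, so the change is worth making although the frequency of switching is unknown.

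**What to change.** State that COWS and HRV scores, and the secondary continuous outcomes, are each analysed by one baseline-adjusted model (ANCOVA, or a mixed model with baseline constrained equal between arms) whatever the normality check shows. Delete the Mann-Whitney sentence or restrict it to named comparisons, and label any rank-based analysis of these outcomes as a sensitivity analysis. Limit the opening rule on distribution and variance in the same way. The survival analysis of time to recovery needs no change on this account.

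Bootstrap inference for skewed residuals and log transformation of HRV measures are optional and can be left to the SAP.

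The cost is a few sentences and a few lines of R code, with no change to sample size, visits or patient procedures. It should be done before outcome data are examined.

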#### **Ethical considerations:**

- Subjects will be informed about all the required procedures of the study and written informed consent will be obtained.
- The investigator will withdraw the subject from participating in the research if; the subject does not fall under the inclusion criteria or if the subject becomes ill during the study.
- The study will be registered under CTRI.
- No financial obligations for the subject. No charges will be collected for the yoga therapy and the assessments.
- Confidentiality of all information will be assured and maintained.
- Subjects will have the right to withdraw consent at any stage.
- Approval from the ethical committee of NIMHANS will be sought.

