## **PROJECT PROPOSAL**

### **Role of Adjuvant Yoga Therapy in Managing Withdrawal Symptoms of Patients with Opioid Use Disorder**

#### **Introduction:**

Opioid use disorder is characterized by chronic use of opioids such as heroin, morphine, codeine, fentanyl, and synthetic opioids like oxycodone which causes clinically significant impairment. It involves an intense desire to use opioids, increased opioid tolerance, and withdrawal syndrome when discontinued. Opioid use disorders affect over 16 million people worldwide and over 120,000 deaths worldwide annually occur due to opioids.(1)

Withdrawal from opioids is characterized by specific problematic behavioral change, with physiologic and cognitive components. The opioid withdrawal syndrome is a collection of clinical signs and symptoms such as hypertension, tachycardia, insomnia, mydriasis, piloerection, lacrimation, excessive sweating, rhinorrhoea, yawning, nausea, vomiting and diarrhea, anxiety, shivering, body aches, easily agitated, craving, hyperactivity, rapid breathing.(2,3) The time course of withdrawal is dependent on the half-life of the opioid used; it may last from 5 to 14 days.(2)

World health organisation recommended three medication treatment for withdrawal symptoms.(4) They are 1) opioid receptor full agonist methadone, 2) opioid receptor antagonist naltrexone 3) opioid receptor partial agonist buprenorphine (available as sublingual or buccal tablets or films, a skin patch). Patients treated with Buprenorphine experienced less severe withdrawal when compared with other drugs(5). Although buprenorphine is an ideal drug of choice, it alone does not control withdrawal symptoms, so ancillary medications such as clonazepam (sedative-hypnotics) for anxiety, trazodone and zolpidem (act via GABA) for sleep, ibuprofen (NSAID) for muscle cramps, bismuth subsalicylate for diarrhea, Ondansetron and prochlorperazine for nausea and vomiting are also used in the management of withdrawal symptoms.(6)

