#### **Objectives:**

- Primary objective:
  1. To evaluate the effect of Yoga on time to recovery from opioid withdrawal symptoms in patients with OUD using the and Clinical Opiate Withdrawal Scale (COWS) and heart rate variability parameters reflecting autonomic regulation.
- Secondary objective:

To access the changes following clinical measures in yoga as an add-on therapy group when compared with the standard treatment-alone group.

  1. Anxiety (HAM-A)
  2. Sleep latency
  3. Brief Pain Inventory

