### **Inclusion criteria:**

- Diagnosis of Opioid use disorder.
- Subjects with mild to moderate severity of withdrawal symptoms (Clinical Opiate Withdrawal Scale: COWS scores between 4 - 24).
- Subjects who got admitted into CAM, NIMHANS and started treatment with Buprenorphine.
- Age range: 18 to 50 years.
- Both genders.
- Written informed consent.

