### Study design:

Patients diagnosed with opioid use disorder are assessed for severity of withdrawal symptoms using Clinical Opiate Withdrawal Scale (COWS). The patients with mild to moderate severity of withdrawal symptoms and taking buprenorphine for management of symptoms are randomized into two groups that is Yoga + standard treatment group and Treatment only group. Duration of intervention is 2 weeks. Clinical history will be done at baseline. Assessments will be done at the baseline and at the end of the intervention, for those who are willing to participate in the study. Safety assessments and adverse events will be monitored and appropriately documented for the duration of study period. The medications prescribed and taken by the patients other than buprenorphine will be documented in both the groups during the study period.

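### Withdrawing from the research any patient who becomes ill loses end-of-intervention outcomes for reasons linked to the outcome; stopping yoga should be kept separate from leaving the study

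*Protocol*

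**What the plan says.** The rule is in the Protocol under Ethical considerations: "The investigator will withdraw the subject from participating in the research if" either of two things applies, namely "the subject does not fall under the inclusion criteria or if the subject becomes ill during the study". It is mandatory, and it takes the patient out of the research as a whole. The Protocol does not define illness and does not provide for any further assessment of a withdrawn patient.

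Four other places bear on it:

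- Objectives. The primary objective is "To evaluate the effect of Yoga on time to recovery from opioid withdrawal symptoms in patients with OUD", measured by COWS and heart rate variability.
- Introduction. The listed signs of opioid withdrawal include "yawning, nausea, vomiting and diarrhea, anxiety, shivering, body aches, easily agitated, craving, hyperactivity, rapid breathing".
- Study design. COWS is rated first, and patients who qualify "are randomized into two groups that is Yoga + standard treatment group and Treatment only group". On timing: "Assessments will be done at the baseline and at the end of the intervention". On safety: "Safety assessments and adverse events will be monitored and appropriately documented for the duration of study period".
- Inclusion criteria. Entry requires "Subjects with mild to moderate severity of withdrawal symptoms (Clinical Opiate Withdrawal Scale: COWS scores between 4 - 24"), so the entry criterion and the primary outcome use the same scale.

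**The concern.** Within two weeks of starting treatment, a patient with vomiting, diarrhoea or shivering may be judged ill, may be doing badly on the primary outcome, or both. A rule that ends research participation for illness therefore tends to stop data collection in patients whose outcome is poor. Only one arm does a physical programme, so the chance of being judged ill, or of illness coming to notice, may also differ by arm.

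At stake are the end-of-intervention COWS, heart rate variability and secondary measures of these patients, and any safety information after they leave. The survival analysis would have to censor them at a moment related to their prognosis. The mixed model would hold only their baseline value and would lean on a missing-at-random assumption that illness-driven withdrawal makes doubtful. An analysis plan can define populations and censoring rules, but it cannot supply measurements that the Protocol had staff stop taking.

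**Working it through.** **What the Protocol fixes.** There are 60 patients, 30 per arm (Methodology), with outcomes at baseline and at two weeks (Study design). No withdrawal rate, alpha, power, effect size or SD is given, so there is no figure of the Protocol's own to reproduce. Everything below is illustration under stated assumptions.

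**Step 1: recovery as a proportion.** Assume 20 of 30 yoga patients recover, so 20/30 = 67%.

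- Only non-recoverers are withdrawn, in one arm only. With 3 withdrawn, 20/27 = 74%. With 6 withdrawn, 20/24 = 83%. The shift is 74.1 − 66.7 = 7.4 points, or 83.3 − 66.7 = 16.7 points, with no true change.
- Withdrawal is unrelated to recovery. If 3 leave, of whom 2 would have recovered, then 18/27 = 67% and the shift is zero.
- The same 40% of non-recoverers leave both arms. Assume 15/30 recover in the control arm. Yoga becomes 20/26 = 76.9% and control 15/24 = 62.5%. The difference falls from 16.7 to 14.4 points, so a true benefit of yoga is understated.

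**Step 2: a continuous outcome.** If the worst share q of a normally distributed outcome is removed from one arm, that arm's mean moves by φ(c)/(1 − q) SD, where c is the upper-q quantile. For q = 0.10, 0.1755/0.90 = 0.195 SD. For q = 0.20, 0.2800/0.80 = 0.350 SD. The sign depends on which arm loses the patients. Equal removal from both arms, with no true effect, gives zero.

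**Step 3: partial dependence, by simulation.** Setting: 30 per arm, t-test at two-sided 5%, 4,000 runs. Correlation means that between illness and outcome.

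| True effect | Withdrawn | Correlation | Result |
|---|---|---|---|
| none | 10% in each arm | 0.5 | no bias; type I error 4.6% |
| none | 20% v 10% | 0.5 | bias 0.08 SD; type I error 5.7% |
| none | 20% v 10% | 1 | bias 0.15 SD; type I error 10.7% |
| none | 20% v 5% | 0.5 | bias 0.12 SD; type I error 6.3% |
| none | 20% v 5% | 1 | bias 0.24 SD; type I error 17% |
| 0.72 SD | one illness threshold for both arms, 10% of controls withdrawn | 0.5 to 1 | estimate 0.68 to 0.58 SD; power 72% to 65% |
| 0.72 SD | one illness threshold for both arms, 20% of controls withdrawn | 0.5 to 1 | estimate 0.65 to 0.50 SD; power 65% to 56% |

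In the rows with no true effect and unequal withdrawal, the arm that loses more patients looks better. In the last two rows yoga works, fewer yoga patients cross the threshold, and the benefit is understated.

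**Step 4: precision alone.** Assume alpha 0.05 two-sided and 80% power. The detectable difference is (1.960 + 0.842) × √(2/n) SD. For n = 30, 27 and 24 per arm this is 0.723, 0.762 and 0.809 SD. For a true difference of 0.723 SD, power falls from 80.0% to 75.7% and 70.7%.

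**The case against.** The strongest reply is that this is one participant-protection sentence in a short inpatient study of adults aged 18 to 50 that already excludes severe medical conditions. Few patients may be affected, and no rate is known. That stands, and it limits how serious the point can be called. It does not remove the point, because the wording is mandatory and uncollected outcomes cannot be recovered.

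A reader might infer more than the text supports:

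- *That recovered patients must be withdrawn because their COWS falls below 4.* The words about the study period attach only to illness. Study design rates COWS before randomising, so the inclusion limb reads most naturally as screen failure. The other reading would remove every recovering patient from a trial of time to recovery. What stands is that this limb has no stated time and should be given one.
- *That withdrawn patients are dropped from the analysis.* The Protocol excludes nobody from analysis and names no analysis population, which is commonly left to the analysis plan. The harm comes from stopping data collection.
- *That the bias favours yoga.* The rule applies to both arms and no rates are given. Steps 1 and 3 show cases in favour of yoga, against it, and with none.
- *That the rule contradicts adverse event monitoring.* It does not. The illness that triggers withdrawal is itself an event to be documented. Only later events could be missed.
- *That unblinded staff decide who is withdrawn.* The Protocol does not say who knows the allocation when that decision is made.

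**Conclusion.** The point holds for the illness limb. Followed as written, the rule leaves ill patients without an outcome after baseline, for reasons that overlap with the primary outcome and may differ by arm. This weakens the randomised comparison and can bias it in either direction.

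The size is not determinable from the Protocol. It runs from zero, if illness is unrelated to outcome and arm, to about 7 to 17 percentage points in recovery. The upper range rests on assumptions: 20 of 30 recover, and 3 to 6 of the 10 non-recoverers in one arm only are withdrawn. It shows what a few patients can do with 30 per arm and is not a forecast. The loss of precision comes on top.

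The conclusion relies on the written assessment schedule. The schematic could not be read; if it shows COWS readings between baseline and the end, less would be lost, though the final assessment still would be.

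The inclusion limb is a matter of clarity: it should be confined to the time before randomisation. Overall this is a cheap improvement.

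**What to change.** Reword the withdrawal sentence under Ethical considerations to say three things:

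1. Eligibility is confirmed before randomisation, and failing the inclusion criteria is a reason not to randomise.
2. A randomised participant who stops the yoga sessions for any reason, including illness, stays in the study. The planned end-of-intervention and safety assessments are done unless the participant withdraws consent.
3. Every randomised participant is analysed in the arm to which he or she was randomised. This may be stated in the analysis plan instead. Reasons for stopping sessions or leaving the study are recorded by arm.

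When illness should stop the sessions is a clinical decision and is not addressed here.

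The cost is a wording change and the follow-up of a few patients who would otherwise be dropped. No stated figure changes; the sample stays at 30 per arm.
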